### Duration of study

The end of study is defined as day 180 after the day of recruitment (day 1). Trial participants will provide data on outcome measures at baseline, and at 3 months and 6 months following recruitment. All data will be submitted via the app.

### Study procedures: Data collection and follow ups

There are no in person follow ups intended in this study, though the patient will be informed that s/he can contact the research team/study clinic at any point during the study. Data will be collected at three time points – at baseline, at month 3 and month 6. All data will be sent in by participants via the app. Appropriate security measures to ensure safe and confidential transfer of data onto a safe haven server have been made.

The trial team will make efforts to ensure that participants respond to the data requests at month 3 and 6. Youth often lead a life full of variety in terms of living arrangements and relationship status. In addition, smart phones might break, be lost, and phone numbers might be changed. Therefore, obtaining data at the required time points could prove a challenge. Participants will consent to a research assistant contacting them, if responses via the app are not received. Three attempts at contact will be made within 10 days of the expected date of receipt. If the participant is not traced/does not respond during this time, he/she will be considered lost to follow up.

### Quality control

SOP for key processes in the study have been developed. Prior to recruitment, the site team will receive extensive training on the objectives, methods and processes of the study. Quality assurance protocols will be set in place to maintain quality of processes in the clinics.

### Database

Data submitted via the app by the participant will be electronically routed onto a database that will be stored on a secure server. At the end of the study this database will be locked prior to analysis.

### Sample size

Sample size has been estimated on the assumption that the smart phone intervention to promote safe sexual practices is expected to increase the self-reported condom use among sexually active youth in Stockholm County by 20% i.e. from 50% to 70%.

The minimum sample size was estimated to be equal to 268, half (*n* = 134) allocated to receive the smart phone application and the other half (*n* = 134) to receive the control. This sample size is sufficient to detect the estimated difference in self-reported condom use between the two groups with 90% power at significant level α = 0, 05. Loss to follow up in similar internet based trials has been reported at a level of 20–40% [31, 32]. Loss to follow up in the present study was calculated at 40% in order to be more conservative. This would imply a final sample size of 446 i.e. 223 in each arm.

### Statistical analysis

Analysis will be based on an intention-to-treat approach. Data will be summarized with descriptive statistics (mean, median, standard deviation, percentiles for numerical variables, frequencies and percentages for categorical variables). Cross tabulations with Chi-Square or Fisher test will be used to test for un-adjusted relationship between binary outcomes and categorical independent variables. For numerical variables t-test, Wilcoxon rank sum test and Kruskal Wallis test will be used to compare mean and medians in two and more groups respectively. A binary logistic regression model will be used to identify significant predictors of binary outcomes. Crude and adjusted odds ratios (OR) with their 95% confidence intervals will be presented. Ordinal or linear regression models will be used to identify significant predictors of numerical outcomes. *P*-value < 0.05 will be considered significant in the final models. Missing values will be filled in (imputed) with a “missing at random” assumption. Sensitivity analysis will be made to explore the effects of departures from the assumptions made in the main analysis. Sub-group analysis, depending on the way on recruitment (clinic or website), and sex will be made.

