## Methods

This study is a multicentre (8 recruiting clinics), parallel group randomised controlled trial. Eligible participants are randomised in a 1:1 allocation ratio to one of two arms: an intervention arm, in which youth receive the interactive application (app) called the ‘Skyddslaget’ or ‘protection team’ app in addition to the standard of care (defined below); and a control arm in which they receive only the standard of care Fig. 1.

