### Randomization

Stratified randomization, separately for male and female participants, will be performed. Within each stratum, block randomization will be used to ensure balanced representation in the two treatment arms (control and intervention) as recruitment progresses. Blocks of 4 and 6 will be used. Randomisation will be done electronically by an interactive web response system at the time of recruitment. Once participants have consented, each participant will be given a study identification number at the site and instructed in the protocols based on their randomisation group. This will allow allocation concealment at the sites.

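### The regressions are framed as a search for significant predictors, and the adjusted arm effect is not tied to the sex stratum, to baseline condom use or to a stated primary result

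*Protocol article*

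**What the plan says.** All of the following is in the protocol article.

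- Statistical analysis, binary outcomes: "A binary logistic regression model will be used to identify significant predictors of binary outcomes".
- Statistical analysis, numerical outcomes: "Ordinal or linear regression models will be used to identify significant predictors of numerical outcomes". This sentence matters more for the primary outcome, which the Outcome assessment section defines as a percentage for each participant.
- The same section promises that "Crude and adjusted odds ratios (OR) with their 95% confidence intervals will be presented". It does not name the adjustment variables or say which estimate is primary.
- Results below the 5% threshold "will be considered significant in the final models". How a model becomes final is not described.
- Randomization: "Stratified randomization, separately for male and female participants, will be performed". In the analysis, sex returns only here: "Sub-group analysis, depending on the way on recruitment (clinic or website), and sex will be made".
- Duration of study: "Trial participants will provide data on outcome measures at baseline, and at 3 months and 6 months following recruitment". No analysis is tied to the baseline values.

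**The concern.** The stated objective is to compare the app with routine care, and "Eligible participants are randomised in a 1:1 allocation ratio to one of two arms". The regression that serves this objective estimates one coefficient, that of arm, with a covariate set chosen beforehand. A search for predictors answers a risk-factor question. If it is carried over into the main analysis, three things are at stake:

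- **Precision.** Baseline condom use is to be collected. If it is prognostic, leaving it out of the arm comparison widens the interval for no return.
- **Analysis as randomised.** Allocation is stratified by sex, and the main comparison should carry that stratum.
- **Which result counts.** A t-test, a rank test, ordinal or linear regression, and crude and adjusted estimates are all allowed. None is named as the primary treatment effect.

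**Working it through.** **1. The plan's own figure.** The Sample size section gives 50% against 70%, 90% power and α = 0.05. Two-sided, with mean proportion 0.6:

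n = [1.960·√(2·0.6·0.4) + 1.2816·√(0.5·0.5 + 0.7·0.3)]² / 0.20² = 124 per arm.

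With the continuity correction, (124/4)·[1 + √(1 + 4/(124·0.20))]² = 134 per arm. This is the stated figure (268 in total). For 40% loss, 268/0.6 = 446.7, against the stated 446. The calculation takes no credit for covariate adjustment.

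**2. What baseline adjustment adds.** The primary outcome is a percentage, so I read the planned 20 points as a difference in means. Let r be the correlation between baseline and follow-up. In a linear model, adjustment multiplies the residual variance by (1 − r²). The documents give neither the SD nor r, so both are assumed. An SD of 0.50 is the largest possible for a quantity between 0 and 1.

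With √(2/134) = 0.1222:

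- Power = Φ(0.20 / [SD·√(1 − r²)·0.1222] − 1.960)
- Difference detectable with 90% power = (1.960 + 1.2816)·SD·√(1 − r²)·0.1222
- n per arm for 90% power = 2·(1.960 + 1.2816)²·SD²·(1 − r²) / 0.20²

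Example at SD 0.50: unadjusted, 0.20/(0.50·0.1222) = 3.274, less 1.960 is 1.314, and Φ = 0.906. At r = 0.5, 3.274/0.866 = 3.781, less 1.960 is 1.821, and Φ = 0.966.

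| r | 1 − r² | n per arm for 90% power, SD 0.50 | Power at 134 per arm, SD 0.50 | Detectable difference, SD 0.50 | Power at 134 per arm, SD 0.40 |
|---|---|---|---|---|---|
| unadjusted | 1 | 132 | 0.906 | 19.8 points | 0.984 |
| 0.3 | 0.91 | 120 | 0.930 | 18.9 points | 0.990 |
| 0.5 | 0.75 | 99 | 0.966 | 17.1 points | 0.997 |
| 0.7 | 0.51 | 67 | 0.996 | 14.1 points | above 0.999 |

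Put another way, 134 adjusted completers per arm are worth 134/0.91 = 147, 134/0.75 = 179 or 134/0.51 = 263 unadjusted ones.

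**3. What sex adds.** The Background section on sexual behaviour reports that 50% of women and 40% of men never or seldom used condoms with a temporary partner. Taking this as a proxy and assuming an equal split by sex, the share of variance explained is 0.25·0.10²/(0.45·0.55) = 0.010. The unadjusted interval is then wider by a factor of 1/√(1 − 0.010) = 1.005, or about 0.5%.

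**4. What a free choice of model could do.** I simulated the null with 134 per arm, a normal outcome and ten candidate covariates: baseline, sex and eight unrelated ones. There were 3,000 replicates at each of r = 0.3, 0.5 and 0.7.

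- Keeping covariates with p < 0.05, arm always in the model: type I error 0.050, 0.051 and 0.049.
- Taking the smallest arm p-value from the crude, pre-specified, selected and full models: 0.070, 0.079 and 0.088.

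The inflation comes from choosing between results, not from selecting covariates around a fixed arm term.

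**The case against.** A reader might infer three stronger charges, and the documents do not support them.

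- **That the arm comparison will not be adjusted.** Adjusted odds ratios are promised, and nothing says that sex or baseline will be left out. A covariate list is commonly left to the statistical analysis plan, which is not shown, so the missing list alone is no finding. This objection stands. What remains is that the article states a purpose for its models, and that purpose is not estimation of the arm effect.
- **That covariates will be picked by p-value and the effect distorted.** No entry or removal rule is stated, and the 5% limit in the final models is a significance threshold. Step 4 shows that such selection, with arm retained, kept type I error near 0.05. The rise to 0.07–0.09 needs a choice of the best result, which the protocol does not propose. This objection also stands.
- **That the trial lacks power.** At the planned 20 points, unadjusted power is 0.906 even at the largest possible SD, which meets the 90% target.

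It is also fair to say that the planned unadjusted tests are a valid comparison of the randomised arms, so forgoing adjustment costs efficiency and introduces no bias. The (1 − r²) result belongs to linear models. It does not carry over to the logistic models, where the adjusted odds ratio is a different, conditional quantity from the crude one.

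**Conclusion.** The point holds as an improvement in precision and pre-specification, below the level of a must-fix error. The regressions are directed at predictors and not at the arm effect. The adjusted analysis is not committed to the stratum or the baseline measure, and no result is named as primary.

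At SD 0.50 and r between 0.3 and 0.7, baseline adjustment removes 9% to 49% of the residual variance and brings the detectable difference from 19.8 points down to between 18.9 and 14.1. At SD 0.40 the power gain at 20 points is slight, because unadjusted power is already 0.984. The size of the benefit therefore rests on assumed values of r and SD, and on reading the 20 points as a difference in mean percentage. The gain from sex alone is small; the reason to include it is to analyse as randomised.

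**What to change.** In the Statistical analysis section, or in the analysis plan if it does not already do so:

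- **Primary outcome.** Pre-specify one linear model of the condom-use percentage over 6 months on arm, sex and baseline condom use. Arm is always retained and no term is selected by significance. Name the arm effect with its 95% interval as the primary result and the crude difference as supportive.
- **Secondary outcomes.** Always include arm and sex. Add the baseline value of the measure where it is collected and not too sparse; for pregnancy and infection it may be too sparse. For binary outcomes, say in advance whether the crude or the adjusted odds ratio is the main one.
- **Predictor modelling.** Keep it if wanted, labelled exploratory and separate from the treatment comparison.

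The cost is wording only. Baseline outcome data are already to be collected, sex is known at randomisation, and the sample size need not change. The text should be settled before the database is locked and before outcomes are seen by arm.

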### Ethical aspects

The study protocol has been ethically approved by institutional ethical review board of the Stockholm region (reference number: 2017/651–31/4). The rights and welfare of the participants will be protected according to the Declaration of Helsinki Ethical Principles for Medical Research Involving Human Subjects. Clinical care and emergency medical services are provided by the participating institutions. Data that is collected as part of the study will be not be linked to any individual, personal identifiers will not be used in data storage, and confidentiality will be maintained at all levels of data management.

Exploring people’s sexual habits and condom use is sensitive information and requires reliable measures to ensure data privacy protection. The Swedish Personal Data Act, 1998:204 is and will be followed throughout the trial. Only members of the research team have access to data collected in the project. Data files are stored on secure servers accessible only on pass worded computers used solely by the researchers. To secure the data transfer from the app, i.e. surveys filled in by participants, all data was encrypted by using a Secure Sockets Layer (SSL) when it was transferred from the app to the server.

### Other studies

We aim to conduct a qualitative study just after the end of the trial. The focus of the qualitative evaluation will be to look deeper into the experience of receiving the smart phone application; what parts of the application might have been perceived as being helpful and what parts might have been intimidating, and why the youth perceived that it did or did not influence their behaviour. We plan to do individual interviews with a sample of youth from the intervention arm and hold focus-group discussions with 6–10 participants in each group.

## Discussion

The popularity of mobile health apps is evident from the estimated 102 billion downloads of health-related apps worldwide [33]. Swedish governmental health strategy strongly supports digitalisation of the health service with a focus on self-managed and remote care [34]. The stigmatised nature of STIs and youth they most affect (almost all young adults in Sweden own a smartphone and are very familiar with digital technology) could suggest that provision of information about STIs, testing and treatment through apps is an effective and highly feasible medium for those at highest risk.

A recent review [33] of current mobile apps for STIs (and genital infections) indicated that few apps meet the needs of people seeking comprehensive, accurate sexual health information and that there was a pressing need for high-quality, easily identifiable apps that address the most common STIs and health concerns. The app to be tested in this trial is developed by public health professionals and clinical staff working in the youth clinics, and it was developed with the input from young people in Stockholm County.

It will provide new information on the level of success with this modality with the youth and also provide information on the strengths and pitfalls of trials partially done over the net in this context.

There has also been recent interest in trials that can be completely or partially conducted over the internet [35]. It is possible to recruit participants, allocate interventions, measure outcomes and enter data using the internet. This trial will have combined traditional trial methods as well as digital app (internet) based trial methods. (See table 1.)

**Table 1 Tab1:** Trial step.

Trial step	Traditional (face to face)	Over the app (internet)
Recruitment	√	√ (net)
Consent	√	
Randomisation		√
Baseline data collection		√
Follow up week 12		√
Follow up week 24		√
End of study communication		√

There are potential advantages and disadvantages of conducting part or all of a randomized trial over the internet. The internet potentially provides researchers with the ability to reach potential participants who would otherwise be unreachable, to access non-clinical populations and to reduce research costs [35]. The advantages of conducting an online trial include the potential to improve the trial’s external validity when an online intervention is being evaluated, and users have the ability to self-refer without having to participate via a health professional; the randomization process has the potential to be more secure, with allocation being concealed [36]. Despite these advantages, the authors indicate that online recruitment could result in unrepresentative samples and multiple registrations and increases the difficulty of verifying identity. They also point to the potential loss of power in the study if participants assigned to the intervention do not receive or fail to complete the intervention, resulting in the true effect of the intervention being underestimated. We are uncertain about the extent to which these problems will affect the current trial. We have tried to anticipate them though, and have put in place protocols for reminders in case of non-response, both of which will be quantified. Loss to follow-up is of particular concern in online trials. Although ours is a mixed trial, we have assumed a large loss to follow up which has been built into the sample size.

In conclusion, this trial attempts to exploit the high mobile phone usage among youth to provide a phone based app intervention in the area of STI, which disproportionately affects youth. If successful, the results will have implications for health service delivery and health promotion among the youth. From a methodological perspective, this trial is also expected to provide important information on the strength and challenges of implementing a partially app (net) based trial in this context.

## Abbreviations

App: Application
*C.trachomatis*: *Chlamydia trachomatis*
HIV: Human immunodeficiency virus
mHealth: Mobile health
MI: Motivational interviewing
SOP: Standard operating procedure
SSL: Secure sockets layer
STI: Sexually transmitted infection
YHC: Youth health clinic
